### **4.2 Primary Objective**

The primary objective is to assess the safety and tolerability of TLN i.v. as weekly administration in patients receiving either escalating doses (up to 14) or multiple equal doses over a period of 8 weeks.

### **4.3 Secondary Objectives**

The secondary objectives of this trial are to assess, if any disease improvement can be observed over the course of the administration of TLN. In addition, information on PK will be collected.

### **4.4 Safety Objectives**

There are no additional safety objectives as the primary objective focuses on safety.

## 5. STUDY OUTCOMES

The outcomes focus on the safety profile of the IMP and a preliminary assessment of the clinical benefit of the drug.

### 5.1 Primary Outcomes

The primary outcome of this trial is safety, designed as the measurement of:

- Occurrence of AEs
- Occurrence of SAEs
- Occurrence of any routine lab test values out of normal range including anti-GM1 antibodies and apolipoprotein B.

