| Clinical Phase:              | Phase I, Safety evaluation                                                                                                                                                                                                                                                                                                                                                                                                                                                                          |
| Background and Rationale:    | The pharmacologically active ingredient of TLN is the membranal lipid Monosialotetrahexosylganglioside or GM1. TLN consists of GM1 associated to a proprietary lipid formulation assembled together as liposomes. Free injections of GM1 have shown to improve the UPDRS-score and therefore the condition of patients with Parkinson's disease. TLN has been developed to improve the delivery of GM1 and its bioavailability and therefore improve the care of Patients with Parkinson's disease. |
| Objective(s):                | The primary objective is: 
 
To demonstrate the safety of TLN administration intravenously in patients with Parkinson's disease.
 
 Secondary objectives are: 
 
Determination of the maximal suitable dose based on safety profile and preliminary efficacy.
 
Determination of the PK profile.
 
                                                                                                  |
| Outcome(s):                  | Primary outcome: Safety, measured as: 
 
Occurrence of AEs
 
Occurrence of SAEs
 
 Secondary outcomes: 
 
Parkinson disease (PD) patients' condition assessed by: Levodopa challenge test (LCT), MDS-UPDRS, PDQ-39, ESS and change in Parkinson's medication (LEDD).
 
Patients' general/mental condition assessed by: BDI, SAS, NMSQuest and MoCA.
 
PK analyses
 
     |

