#### 3.4.3 Clinical safety of GM1

The clinical tolerability profile of GM1 is extremely positive. So far, there are no indications of acute or long-term cumulative toxicity. Intravenous single doses of 2500 mg GM1 showed no acute clinical side effects. The repeated parenteral administration of high doses of GM1 (up to 2500 mg/day on 5 days per week each) resulted in increased cholesterol and triglyceride levels and an increase in

apolipoprotein B in healthy volunteers after 4 weeks. All changes were regredient after treatment was stopped. Apart from the above-mentioned laboratory readouts changes, no other effects were observed. Over the total of the above mentioned 51 clinical studies the AEs reported are local pain during i.m. injections, rash and other skin reactions, exfoliative dermatitis, severe allergic reaction in one patient, hyperlipidaemia without a clear causal relationship to GM1. Furthermore, these AEs were only observed sporadically and inconsistently. Among all of the patients, one patient developed a symptom consistent with Guillain-Barré syndrome (GBS). This patient suffered a stroke before treatment with GM1 and had a long medical history including alcohol abuse, atrial fibrillation, congestive heart failure, angina, liver insufficiency, diabetes and chronic symmetric sensory neuropathy. The most reproducible AEs during long-term treatment of PD patients so far were found with 100 mg b.i.d. GM1 s.c. over a period of 2.5 to 5 years and were limited to local injection reactions such as redness and swelling.

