## 9.2 Assessments of outcomes

### 9.2.1 Assessment of primary outcome

Clinical AEs, lab values and vital signs, will be assessed during each visit as reflected in the two schedules (part 1 and part 2 of the trial). In addition, patients will also be asked to contact the PI's practice if they experience any adverse effect between visits, to assess if this could be related to the treatment and would require further medical attention and if any actions are to be taken. Patients will be asked to provide as much detail as possible at the time of the visit. Details should include the time and duration of these occurrences that will be examined with the investigator to fill the weekly reporting of AE. The investigator will document the AEs in the eCRF after each visit and will notify the sponsor in case of SAEs. All AEs and SAEs will be documented as follows: time of onset, duration, resolution, action to be taken, assessment of intensity, relationship with trial treatment (for all details refer to section **10 SAFETY**). Pre-existing signs and symptoms, especially of PD, are not to be considered an AE. Parkinsonian signs and symptoms are considered an AE in this trial if they appear to be new or if a previously present non-fluctuating symptom clearly worsens. A fluctuating parkinsonian symptom will only be counted as an AE if the fluctuation clearly increases in frequency or duration or if the extent of the fluctuating symptom at its worst is clearly worse compared to the baseline condition.

In order to assess other safety issues, blood samples will be taken and analysed for routine assessments (termed full lab tests thereafter) to assess if TLN modifies the blood cell count, the electrolytes, metabolites and liver markers (for the full list of lab tests and standard values see the **Annexes 1 & 2**) or result in an elevation of anti-GM1 antibodies or apolipoprotein B (a marker of hyperlipidaemia).

The full lab tests consist of:

- 1- The "routine" lab analyses will be performed (Cat #: Rout-3549)
- 2- Anti-GM1 IgG antibodies (Cat #: gm1g 52250)
- 3- Apolipoprotein B (Cat #: apob-7320) assays

All required material will be provided by Viollier. 4 tubes (3 x 0.5 ml of blood serum-gel-tube and 1 x 0.5 ml of blood in EDTA tube) will be required for these tests from each patient.

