Safety lab values will be assessed from blood collection performed every week during part 1 (3 days after TLN infusion) and part 2 (on the day of TLN infusion) according to the schedule. Abnormal

values will be compared to the normal range provided by the laboratory (**Annex 2**), then assessed by the PI for grading. All analyses will be performed from venous blood collection before the infusion. Samples will be collected on each sampling day by courier by Viollier and processed in their facilities.

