| Triglyzeride                         | < 1.14 mmol/L          | 0 - 12 Y  | f+m |
|                                      | < 1.71 mmol/L          | 13 - 19 Y | f+m |
| Cholesterin gesamt                   | < 5.00 mmol/L          |           | f+m |
| HbA1c (IFCC)                         | < 42.0 mmol/mol        |           | f+m |
| HbA1c (NGSP)                         | < 6.1 %                |           | f+m |
| Amylase pankreasspezifisch           | 13 – 53 U/L            |           | f+m |

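### The laboratory part of the primary outcome ignores pre-dose values, so a per-patient rate would be near saturation without any drug effect

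*Protocol*

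**What the plan says.** Section 5.1 of the protocol gives three primary safety outcomes: adverse events, serious adverse events, and "Occurrence of any routine lab test values out of normal range including anti-GM1 antibodies and apolipoprotein B". The third carries no baseline condition, no severity threshold and no list of analytes of main interest.

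Section 9.2.1 states the purpose of the blood tests: "to assess if TLN modifies the blood cell count, the electrolytes, metabolites and liver markers", or whether anti-GM1 antibodies or apolipoprotein B rise. On the comparison itself, it says that abnormal "values will be compared to the normal range provided by the laboratory", after which the investigator grades them. The patient's own pre-dose result is not mentioned. On timing: "Safety lab values will be assessed from blood collection performed every week during part 1 (3 days after TLN infusion) and part 2" (in Part 2, on the infusion day).

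Full panels are drawn at screening and on day 0 in both parts (9.3.1, 9.3.2, 9.3.7, 9.3.8). Section 7.1 has no criterion requiring normal laboratory values. Section 11.4.2 lists laboratory data among the key safety data, tabulated by cohort and, where applicable, dose level.

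The synopsis stops at AEs and "Occurrence of SAEs" under primary outcome and has no laboratory component.

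**The concern.** Whether TLN modifies a marker is a question about change. Whether any value lies outside the laboratory's range is a question about status, and status depends on the number of tests and on abnormalities present before dosing. With a large panel, weekly draws, 12 patients and no control arm, a yes/no status count can sit near its ceiling whatever the drug does.

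The protocol handles comparable items differently. In 9.2.1 parkinsonian signs count as adverse events only if new or clearly worse. In 5.2 the levodopa challenge test, PDQ-39 and ESS are differences from baseline.

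Lipids matter most here, because section 3.4.3 reports that repeated high GM1 doses led to "increased cholesterol and triglyceride levels" and to higher apolipoprotein B. Annex 2 sets single upper limits for LDL cholesterol (3.00 mmol/L) and total cholesterol (5.00 mmol/L). Patients already above a limit before dosing would be counted whether or not TLN raised their values.

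**Working it through.** The protocol gives no expected abnormality rate and no formal sample size calculation (11.2), so there is no stated figure to reproduce. The check asks how often the 5.1 rule would be met with **no drug effect**.

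**Inputs from the protocol**
- Analytes: Annex 1 lists 41 routine items; anti-GM1 IgG and apolipoprotein B make 43.
- Draws after the first dose, Part 2: visits 8 to 14 (7) + final assessment + follow-up = 9 (9.3.11 to 9.3.13). The day 1 sample is excluded because 9.2.1 takes blood before the infusion.
- Draws after the first dose, Part 1: visits 4, 6, …, 28 (13) + final assessment + follow-up = up to 15 (9.3.4 to 9.3.6).

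**Assumptions (not in the protocol)**
- Chance *p* that an unaffected value is out of range: 2.5% to 5% per analyte.
- Correlation between analytes: 0 to 0.5. Within-patient persistence (ICC): 0.5 to 0.8.

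**Closed form**, P(at least one flag) = 1 − (1 − p)^k:
- One draw, 43 independent analytes: 1 − 0.95^43 = 89%; 1 − 0.975^43 = 66%.
- One draw, if the panel behaves like only 10 independent tests: 1 − 0.95^10 = 40%; 1 − 0.975^10 = 22%.
- The same 10 tests over 9 independent draws: 1 − 0.95^90 = 99%; 1 − 0.975^90 = 90%.

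Weekly draws in one patient are not independent, so a multivariate normal simulation was also run, with 43 analytes, one baseline draw and 9 later draws.

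| Correlation | ICC | p | Flagged at baseline | Any flag after dosing | Any *new* flag |
|---|---|---|---|---|---|
| 0 | 0.5 | 5% | 89% | 100% | 100% |
| 0.3 | 0.8 | 5% | 76% | 99.6% | 98% |
| 0.3 | 0.8 | 2.5% | 52% | 93% | 89% |
| 0.5 | 0.8 | 5% | 59% | 97% | 94% |
| 0.5 | 0.8 | 2.5% | 37% | 83% | 79% |

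Over all 12 combinations tried, any flag after dosing ran from 83% to 100%, and any new flag (in range at baseline, out later) from 79% to 100%. Part 1 with 15 draws, at correlation 0.3, ICC 0.8 and p = 5%, gave 99.9%.

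**Subsets** (9 draws, correlation 0.5, ICC 0.8; every limit modelled as one-sided upper, a simplification for HDL), no effect versus a 1 SD rise in all analytes of the subset:
- Six lipid analytes: 44% vs 87% if 5% of unaffected values exceed each limit; 81% vs 98% if 20% do; 98% vs 99.9% if 50% do.
- Five liver analytes: 25% vs 74% at 2.5%; 40% vs 85% at 5%; 58% vs 93% at 10%.

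**What a change measure could do.** One analyte, one pre-dose and one post-dose value, n = 9, two-sided 5% paired t-test, SD of the difference = √(2(1 − ICC)) in between-plus-within SD units:
- ICC 0.8: SD of difference 0.63; power 55% for a 0.5 SD shift and 98.5% for 1 SD.
- ICC 0.5: SD of difference 1.00; power 26% and 75%.

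**Annex 2.** In the text available, the row headed "Triglyzeride" shows limits only for ages 0 to 12 and 13 to 19, while section 7.1 admits patients aged 40 to 80. Other rows of the annex are visibly damaged by text extraction, so an adult row may simply have been lost.

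**The case against.** The protocol never says that it will compute a pooled per-patient yes/no rate. Section 11.4.2 only promises tabulation, the trial has no hypothesis (11.1), and no dosing decision uses a laboratory flag rate: section 8.3 works on causality and grade. Abnormal values are graded by the investigator, and an abnormal finding can be an adverse event under 10.1, with causality assessment and weekly committee review. Shift tables are commonly left to the statistical analysis plan, which is not at hand. All of this stands, and it limits the consequence. It does not change the fact that 5.1 states the primary outcome as an occurrence of any out-of-range value, or that a rate built on that statement would carry little information.

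A reader might infer that a TLN effect on lipids or liver could not be told from background in this trial. The documents do not support that. Two pre-dose panels and weekly repeats allow within-patient comparison, the liver subset does not saturate, and a 1 SD change in a single analyte would often be detectable with nine patients. A reader might also infer that triglycerides cannot be classified at all. That is unproven, given the possible extraction loss and the reference in 9.2.1 to the laboratory's own range.

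The assumed rates are also open to challenge. Many Annex 2 limits are one-sided, and no figure for lipid abnormality before dosing is given. Hence the ranges: the single-draw figure can be as low as 22%, but the figure over 9 correlated draws did not fall below 83%.

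**Conclusion.** The point holds for the outcome as defined, not for the trial's laboratory data as a whole. On the 5.1 definition, about 83% to 100% of Part 2 patients would score with no drug effect, and 36% to 89% would already be flagged before dosing. These figures rest on the assumed out-of-range rates, correlations and ICCs listed above. The rate therefore says little on the question posed in 9.2.1. It is least informative for lipids if many patients exceed the cholesterol limits at entry, which the protocol neither states nor excludes.

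The mismatch between the synopsis and 5.1 on the number of primary outcomes is a plain contradiction and needs no assumption. The triglyceride limit is a point to confirm, not an established error.

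**What to change.** 1. In 5.1 and 11.4.2, define the laboratory outcome as change, or shift in category or grade, from the pre-dose value, analyte by analyte. Name the measures of main interest: the lipids including apolipoprotein B, the liver analytes and anti-GM1 antibodies. State which pre-dose value (screening, day 0 or both) is the reference.
2. Do not replace the present rule with a pooled flag for any new abnormality; it still scores about 79% to 100% of patients with no effect.
3. Make the synopsis list the same primary outcomes as 5.1.
4. Confirm that Annex 2 contains the laboratory's adult triglyceride limit, and add it if it does not.

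The cost is wording and somewhat more tabulation. No additional blood is needed, since the pre-dose panels are already scheduled. The trial would no longer report a single overall out-of-range rate.

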### 5.2 Secondary Outcomes

The secondary outcomes are PD related and will consist in assessing the overall clinical performance during the course of the trial.

They will consist of the following measurements:

- Cognitive assessment (MoCA) to be assessed at baseline and the final assessment (1 week after the last TLN infusion). Two different versions of the MoCA will be used to limit test-retest-learning bias.
- Levodopa challenge test (LCT): Change in LCT between baseline assessment and the final assessment (1 week after the last TLN infusion).
- MDS-UPDRS: Evolution with time of the MDS-UPDRS performed at the time of each infusion (weekly), at the final assessment (1 week after the last TLN infusion) and during follow-up visit (4 weeks after the last TLN infusion).
- MDS-UPDRS-3 motor assessment (as part of the MDS-UPDRS) before and after the TLN infusion to assess if there is an immediate (symptomatic) effect of TLN on parkinsonian motor signs.
- PDQ-39: Difference in PDQ-39 summary index between baseline assessment and the final assessment (1 week after the last TLN infusion).
- ESS: Change in ESS between baseline assessment and the final assessment (1 week after the last TLN infusion).
- Mood/depression assessment by BDI. Measured at baseline and the final assessment (1 week after the last TLN infusion).
- Assessment of motivation/apathy with the SAS at baseline and the final assessment (1 week after the last TLN infusion).
- The Non-Motor Symptoms Questionnaire (NMSQuest) will be measured at baseline and weekly during the course of the trial.
- Levodopa equivalent daily dose (LEDD) will be calculated at each assessment visit.
- Pharmacokinetic (PK) of total GM1 in plasma over the first 96 h after the first infusion (only in part 2 of the trial).
- Determination of a maximum suitable dose (MSD).

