## 7. STUDY POPULATION

### 7.1 Eligibility criteria

Participants fulfilling all of the following inclusion criteria are eligible for the trial:

1. Informed consent as documented by signature.
2. Male and female subjects, aged 40 to 80 years.
3. Confirmed Parkinson's disease according to British brain bank criteria.
4. Hoehn and Yahr Stage 0 – 2.5 on medication.
5. Stable PD treatment for 4 weeks at least.
6. Absence of dementia confirmed by cognitive testing (MoCA >25).

The presence of any one of the following exclusion criteria will lead to exclusion of the participant:

1. Contraindications to the class of drugs under study, e.g., known hypersensitivity or allergy to class of drugs or the investigational product.
2. Women who are pregnant or breast feeding, or planning to become pregnant during the course of the trial or in the 12 weeks following the trial.
3. Lack of safe contraception, defined as:
  - Female participants of childbearing potential, not willing to use double method of contraception (hormonal and mechanical) for the entire study duration. Female participants who are surgically sterilised / hysterectomised or post-menopausal for longer than 2 years are not considered as being of child bearing potential.
  - Male participants, not using and not willing to using a medically reliable method of contraception for the entire study duration, such as condoms or who are not using any other method considered sufficiently reliable by the investigator in individual cases.
4. Other clinically significant concomitant disease states (e.g., renal failure, hepatic dysfunction, cardiovascular disease etc.) that are not under stable control.
5. Known or suspected non-compliance, drug or alcohol abuse.
6. Inability to follow the procedures of the trial, e.g., due to language problems, psychological disorders etc. of the participant.
7. Participation in another trial with an investigational drug 4 weeks prior to the present trial.
8. Previous enrolment into the current trial.
9. Enrolment of the investigator, his/her family members, employees and other dependent persons.
10. Subject has an atypical parkinsonian syndrome or secondary parkinsonism.
11. Patients with comorbidity that may interfere with the course of the trial.
12. Patients who are not considered to be eligible to participate in clinical trial by the investigator.

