## **Dose consolidation (part 2)**

### **9.3.7 Visit 1: Screening (between day -28 until day -1)**

All patients will be screened by the PI. Patients willing to sign the informed consent form will be informed orally and in writing in detail about the exact procedures, their rights and duties. They will especially be informed that some screening assessments need to be done in order to decide if eligibility criteria are met.

- Explanation of the trial (risk/benefit) to the patients (60-120 min). Patient information is handed out in writing.
- Checking of all in- and exclusion criteria (10 min)
- Evaluation of the patient's medical history (10 min)

If inclusion and exclusion criteria are met as far as can be ascertained so far, and if at least 24 h have passed since patient information was given, written informed consent is signed by the participant and the PI. Then the following baseline assessments are performed:

- Pregnancy test for female patients with childbearing potential (blood test hCG).
- Clinical assessment (including physical medical and neurological exam, height and weight).
- Vital signs
- MoCA (20 min)
- Full lab tests

If all inclusion and exclusion criteria are still met, the patient is included in the trial, otherwise a screening failure is declared.

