### **9.3.8 Visit 2: Baseline (day 0)**

- Vital signs
- Full lab tests
- LCT
- PDQ-39
- ESS
- BDI
- SAS
- NMSQuest
- LEDD

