## 11. STATISTICAL METHODS

The present section outlines the statistical principles for the planned analyses of this phase I trial. The analysis will be exploratory and primarily employ descriptive statistical methods. Inferential methods will be used to highlight interesting aspects of the data. Unless otherwise specified statistical tests will be two sided and conducted at the 5% significance level. Corresponding 95%-confidence intervals will be presented and no correction for multiplicity will be applied.

Additional analyses may be defined before DB lock at the end of the treatment phase or during the execution of the planned analysis or after its completion.

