#### 11.4.3 Secondary Analyses

Efficacy analyses will be conducted in the Efficacy Analysis Set. In addition to descriptive summaries of efficacy parameters over time by dose/cohort, for patients in the multiple dose part, a statistical comparison of the change from baseline to the last visit will be performed, e.g., by means of the Wilcoxon signed-rank test for continuous variables. The evolution over time will also be analysed: the choice for the specific model (e.g., mixed-models for repeated measures or random coefficients

models) will be made at the time of analysis-based considerations such as the distribution and timing of observations or missing data patterns.

PK analyses will be descriptive and PK parameters will be derived directly from the plasma concentration-time curves or calculated using non-compartmental methods.

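### The only pre-dose MoCA is the screening score that had to exceed 25 for entry, so selection alone biases the MoCA change from baseline downward

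*Protocol*

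**What the plan says.** Section 5.2 lists MoCA among the secondary outcomes: "Cognitive assessment (MoCA) to be assessed at baseline and the final assessment (1 week after the last TLN infusion"). It adds that two versions of the test will be used to limit learning bias.

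Section 7.1 makes the same instrument an inclusion criterion: "Absence of dementia confirmed by cognitive testing (MoCA >25").

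The visit lists show which score serves both purposes. Sections 9.3.1 (part 1) and 9.3.7 (part 2) introduce the Visit 1 tests, MoCA among them, with "Then the following baseline assessments are performed". The same sections close with "If all inclusion and exclusion criteria are still met, the patient is included in the trial, otherwise a screening failure is declared". The lists for Visit 2 in 9.3.2 and 9.3.8 contain PDQ-39, ESS, BDI and SAS but no MoCA. In the part 2 schedule table the MoCA row is marked only at screening and at the final assessment.

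For the part 2 patients, section 11.4.3 states that "a statistical comparison of the change from baseline to the last visit will be performed, e.g., by means of the Wilcoxon signed-rank test". Section 11 adds that, unless otherwise specified, "statistical tests will be two sided and conducted at the 5% significance level", with 95% confidence intervals and no multiplicity correction. Section 11.2 plans nine patients for part 2. There is no control group.

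**The concern.** A MoCA score is a true level plus measurement error. Admitting patients because the observed score exceeds 25 favours those whose error on that day was positive. At the final assessment the error is drawn afresh, so with no drug effect and no practice gain the expected change is below zero. A test or confidence interval for change that takes zero as the no-effect value then starts from the wrong place. The two versions mentioned in 5.2 address learning, not selection.

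PDQ-39, ESS, BDI and SAS take their baseline at Visit 2 and are not entry gates, so MoCA differs from them in this respect. It is also the only cognitive test on the schedule. Section 3.7 mentions confusion and disorientation as possible effects of TLN, and the trial is meant to inform a phase II plan. A shift created by the visit schedule could be read as a drug effect, or could hide a real gain. A statistical analysis plan can change the test but cannot recover a baseline score that was never collected.

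**Working it through.** **Inputs from the protocol.** Entry cut-off: MoCA above 25, that is 26 or more on an integer scale (7.1). Tested part: n = 9 (11.2). Test: two-sided 5% (11), signed-rank given as an example (11.4.3). Control group: none.

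**Inputs not in the protocol, therefore assumed.** Mean of the screened patients 25 to 27; SD 2.5 to 3; test-retest reliability r from 0.60 to 0.90; residual practice gain 0, 0.5 or 1 point. The plan states no MoCA mean, SD, reliability or expected change, so it has no figure to reproduce.

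**Formula (no drug effect, no practice gain).** With a = (25.5 - mean)/SD,

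expected change = -(1 - r) × SD × φ(a) / [1 - Φ(a)].

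- Mean 26, SD 3, r 0.75: a = -0.167, φ = 0.393, 1 - Φ = 0.566, ratio 0.695; 0.25 × 3 × 0.695 gives -0.52.
- Mean 25, SD 3, r 0.60: a = 0.167, φ = 0.393, 1 - Φ = 0.434, ratio 0.907; 0.40 × 3 × 0.907 gives -1.09.
- Mean 27, SD 2.5, r 0.90: a = -0.60, φ = 0.333, 1 - Φ = 0.726, ratio 0.459; 0.10 × 2.5 × 0.459 gives -0.11.

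**Simulation.** Integer scores capped at 30, entry on the first score, no drug effect, exact signed-rank test with n = 9, 3,000 trials per setting. Results for SD 3:

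| Mean | r | Share passing | Formula | Change, no gain | Rejections, no gain | Change, gain 0.5 | Change, gain 1 |
|---|---|---|---|---|---|---|---|
| 25 | 0.60 | 0.44 | -1.09 | -1.12 | 18.7% | -0.67 | -0.24 |
| 25 | 0.75 | 0.43 | -0.68 | -0.70 | 9.8% | -0.27 | +0.14 |
| 25 | 0.90 | 0.43 | -0.27 | -0.29 | 3.4% | +0.14 | +0.55 |
| 26 | 0.60 | 0.57 | -0.83 | -0.85 | 11.2% | -0.43 | -0.05 |
| 26 | 0.75 | 0.57 | -0.52 | -0.54 | 5.5% | -0.13 | +0.25 |
| 26 | 0.90 | 0.57 | -0.21 | -0.22 | 2.6% | +0.18 | +0.55 |
| 27 | 0.60 | 0.69 | -0.61 | -0.61 | 6.3% | -0.24 | +0.10 |
| 27 | 0.75 | 0.69 | -0.38 | -0.39 | 3.8% | -0.02 | +0.32 |
| 27 | 0.90 | 0.69 | -0.15 | -0.17 | 2.0% | +0.20 | +0.54 |

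With SD 2.5, mean 25 and r 0.60 give -0.96 and about 16% to 17%; mean 27 and r 0.90 give -0.13 and about 1.5%. A repeat of the first table row gave 16.7% instead of 18.7%, so the upper end is about 17%, or 19% in one run. Where the rate exceeds 5%, nearly all rejections are declines.

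On a wider grid of 24 settings (mean 25 to 28, SD 2 or 3, the same reliabilities), the change without practice gain is negative in all 24, from -0.05 to -1.12. The rejection rate exceeds 5% in 8, all with r of 0.60 or 0.75. The net change is still negative in 10 of 24 with a gain of 0.5 point and in 2 of 24 with a gain of 1 point.

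**Check of the remedy.** With a separate score not used for selection as the baseline, and no practice gain, the mean change is about 0 and the rejection rate about 1% to 4%.

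**The case against.** A reader might infer that 5.2 contradicts the schedule, because "Visit 2: Baseline (day 0") has no MoCA. The documents do not support this. Sections 9.3.1 and 9.3.7 themselves count the screening tests as baseline assessments, so the Visit 1 score is the baseline as planned. A MoCA at Visit 2 would be a new request, not compliance with 5.2.

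A reader might also infer that the trial will show a false cognitive decline. That goes too far. Section 5.2 claims only to limit learning, and a residual practice gain of 0.5 to 1 point can cancel or reverse the shift. The larger rates also need many patients near the cut-off: at a mean of 25 only about 40% to 44% of those tested would pass. Section 7.2 has patients identified against the criteria beforehand, which may make MoCA screen failures rarer and the bias smaller.

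The safety link is weak too. Section 3.7 judges the encephalopathic risk minimal, confusion would be recorded as an adverse event, and section 8.3 acts on grade and causality, not on MoCA.

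Finally, the analysis is exploratory, the signed-rank test is only an example for continuous variables, and 5.2 specifies a change or difference for LCT, PDQ-39 and ESS but not for MoCA. All of this stands and lowers the weight. It does not remove the point: the estimated change and its interval carry the selection bias whichever test is chosen, and an unknown practice gain cannot be relied on to cancel an unknown selection effect.

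**Conclusion.** The point holds as a modest one on an exploratory secondary outcome. The score that admits the patient is also the reference for change, it is not repeated before dosing, and no control group absorbs the regression to the mean. The direction of the selection bias is certain; its size is not derivable from the protocol. Under the assumptions above and without practice gain it is roughly -0.1 to -1 point, with a false-positive rate of about 1% to 17% at n = 9. That rate exceeds 5% only when the screened mean lies near the cut-off and reliability is moderate or low. With a practice gain the net sign is uncertain, so neither an apparent decline nor a false safety signal can be predicted. The primary safety outcome and the dose rules are not touched.

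**What to change.** For patients still to be enrolled, add a MoCA in a further parallel version at Visit 2 (day 0). State in 5.2 and 11.4.3 that this score is the baseline for change, and keep the Visit 1 score for eligibility only. The cost is about 15 to 20 minutes at an existing visit, one more version than the two now planned, and some added practice exposure. This removes the selection bias but not any practice gain up to the final assessment, which should be acknowledged when the result is read.

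Alternatively, exclude MoCA from the change-from-baseline testing in 11.4.3 and report individual scores descriptively. State that the first score was the entry gate and that the change is subject to regression to the mean. Do not quote a fixed expected fall, because the documents give no basis for one. This costs only a change of wording.
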